  1. SECONDARY OBJECTIVES

1. To what extent can value of care variation in care be identified from ePROMs and ePREMs surveys?

- What is the share of suspected low-value care and suspected high-value care in Germany, per indication and in subgroups?
- How do ePROM and ePREM results differ according to age, gender, indication, city/state, healthcare system utilization (changes in frequency of outpatient practitioner attendance, prescriptions, hospitalizations, etc.), and DMP participation?
- Can ePROMs and ePREMs function as an early warning signal for deteriorating chronic conditions or adverse events such as hospital admission?

1. What are the benefits or drawbacks of PRO feedback (outcome reports) sent to patients?

- Are the PRO value reports understandable to patients?
- Can PRO feedback function as a positive nudge (lead to positive behavioral changes e.g., healthier or more active lifestyle, more active participation in medical treatment, actively approaching treating physicians in the office setting)?
- Are there any negative emotional reactions when receiving PRO feedback that shows values worse than those of a comparable group?

1. Background/Introduction

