**Patient reported indicators:**

- Generic PROM index score: PROMIS PROPr is a preference-based score which combines seven PROMIS domains of health status into one score (cognitive function, depression, fatigue, pain, physical function, sleep, social roles)
- Disease-specific PROM index scores for each chronic disease

Asthma: Asthma Impairment and Risk Questionnaire (AIRQ) score

COPD: Clinical COPD Questionnaire (CCQ) score

Diabetes: Problem Areas in Diabetes (PAID-5) score

Coronary artery disease: Seattle Angina Questionnaire (SAQ-7) score and Rose Dyspnea Scale (RDS) score

- PREM index score: Responsiveness of the health care system
- Looked at PRO feedback
- Comprehensibility of PRO feedback
- Helpfulness of PRO feedback
- Emotional reaction to PRO feedback
- Discussion of PRO feedback with physician(s)
- Health behavior in five dimensions:

Physical activity

Nutrition

Tobacco consumption

Alcohol consumption

Sleep duration

- Plans to change health behavior in the future
- Trigger for health behavioral change
- Overall health improvement
- Disease-specific health improvement

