- Using machine learning predictive models (long-short-term memory deep learning network for time trend classification, random forest, logistic regression, decision tree and/or support vector machine) to identify admission risk in Q3 and Q4 based on PROMs/PREMs in Q1 and Q2

*PRO feedback*

- Mainly: Statistically significant change in at least one of the health care behavior dimensions (see 4.2) and comparison of participants who opened the report vs. those who did not, using logistic regression (change/no change)
  - Physical activity: Shift of participants to a higher category
  - Nutrition: Shift of participants to “More healthy” from any other category
  - Tobacco: Shift of participants to a lower category
  - Alcohol: Shift of participants to a lower category
  - Sleep: Share of stable participants (no significant variation in sleep duration)
- Secondly: Descriptive exploratory analysis of the rates of the following two evaluation dimensions and statistically significant differences in subgroups (see 5.1 and 4.3):
  - Understandability
  - Helpfulness
  - Emotional change

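### Sleep is scored as absence of change inside an outcome defined as change in at least one health behaviour, and how stable sleepers are coded is not stated

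*Protocol*

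**What the plan says.** Protocol 5.2, under Secondary Outcomes, PRO feedback, opens with "Mainly: Statistically significant change in at least one of the health care behavior dimensions (see 4.2" and adds a "comparison of participants who opened the report vs. those who did not, using logistic regression (change/no change"). Five sub-items then say what counts in each behaviour. Activity reads "Physical activity: Shift of participants to a higher category" and tobacco reads "Tobacco: Shift of participants to a lower category". Alcohol is worded like tobacco, and nutrition counts a move into the healthier category. All four are shifts in a favourable direction. Sleep instead reads "Sleep: Share of stable participants (no significant variation in sleep duration").

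Two other places bear on this. The list of patient-reported indicators in 2.6 has "Health behavior in five dimensions", with sleep duration as one of them. The objective being served, in 1.2, asks "Can PRO feedback function as a positive nudge (lead to positive behavioral changes").

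The protocol does not say whether a stable sleeper is coded as change or no change, what counts as significant variation for one person, which change in sleep duration is an improvement, or what share of participants is expected to be stable.

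**The concern.** An item that is satisfied by not changing sits inside an outcome defined as change, next to four items that require a favourable change. The sleep rule also ignores level. Someone who sleeps too little in every survey satisfies it, and someone whose short sleep lengthens does not.

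This is the main analysis of whether the report works as a nudge (third research question). If the sleep item enters a per-person at-least-one variable as written, many participants meet the outcome without changing any behaviour. The contrast between openers and non-openers then shrinks, and its sign can depend on which way sleep moves. The protocol fixes a rule here, and that rule contradicts the outcome it belongs to, so this is more than detail deferred to an analysis plan.

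**Working it through.** **Stated figure.** The protocol gives no rate, effect size or power for this outcome. Its only related figure is the expected number of complete data sets (2.5): 200,000 × 0.30 × 2/3 × 0.40 = 16,000, which reproduces exactly.

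**Possible codings of the sleep item.** The text does not choose among these.
1. Stable counts as meeting the outcome, in parallel with the other four sub-items. No change is then scored as change.
2. Stable is coded as no change. The sub-item then runs opposite to the other four, and any variation, including worsening, could count as change.
3. Stability is only a group-level share. It then cannot enter a participant-level logistic regression, although it is listed under one.

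**Size under coding 1, with a per-person outcome.** Assumptions, none from the protocol: stable share s; chance p of a favourable shift in each of the other four behaviours; independence; s equal in openers and non-openers.
- Without sleep: P = 1 - (1 - p)^4.
- With sleep: P = 1 - (1 - s)(1 - p)^4.
- Difference without sleep: (1 - p0)^4 - (1 - p1)^4, where p0 is for non-openers and p1 for openers. With sleep it is the same expression times (1 - s), whatever p0 and p1 are.

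Share meeting the outcome, for p from 0.05 to 0.20:

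| s | Share meeting it |
|---|---|
| sleep left out | 18.5% to 59.0% |
| 0.50 | 59% to 80% |
| 0.60 | 67% to 84% |
| 0.70 | 76% to 88% |
| 0.80 | 84% to 92% |
| 0.90 | 92% to 96% |

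**Dilution example.** Let p rise from 0.10 to 0.12 in each of the other four behaviours, with no effect on sleep. Without sleep: 1 - 0.90^4 = 34.4% and 1 - 0.88^4 = 40.0%, a difference of 5.6 points. Sample size is per group for 80% power at two-sided 0.05.

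| s | Difference (points) | Per group |
|---|---|---|
| sleep left out | 5.6 | 1,152 |
| 0.50 | 2.8 | 4,250 |
| 0.60 | 2.3 | 5,799 |
| 0.80 | 1.1 | 13,545 |
| 0.90 | 0.6 | 29,035 |

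At s = 0.80, two groups of 13,545 make 27,090, against 16,000 expected complete participants before any split into openers and non-openers. On the odds-ratio scale of the planned model, the same example falls from (0.4003/0.5997)/(0.3439/0.6561) = 1.27 to (0.8801/0.1199)/(0.8688/0.1312) = 1.11 at s = 0.80.

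**Direction.** Keep p = 0.10 in both groups and let the report affect sleep only, by 5 percentage points.

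| s | Stable to improved: OR | Worsened to stable: OR |
|---|---|---|
| 0.60 | 0.85 | 1.19 |
| 0.80 | 0.77 | 1.38 |
| 0.90 | 0.64 | 2.07 |

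For s = 0.80, the first case is 86.9% falling to 83.6% and the second is 86.9% rising to 90.2%. A move from worsened straight to improved leaves the sleep item unchanged.

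With a benefit in the other behaviours as well (OR 1.3 each, p from 0.05 to 0.20, s from 0.70 to 0.90, 12 combinations), the composite OR depends on how many openers leave the stable group:
- None: 1.07 to 1.30, never below 1.
- 2 points: 0.87 to 1.21, below 1 in 5 of 12.
- 5 points: 0.68 to 1.09, below 1 in 9 of 12.

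**The case against.** The strongest reply is that the per-person composite is one reading only. Statistical significance is a property of a group test, and the sub-items speak of shifts and shares of participants. The line in 5.2 could therefore mean five separate analyses, with success if any one is significant. Section 4.2 lists the impact on behaviour both overall and by subdimension, which supports this. On that reading there is no composite to dilute, and only the odd sleep definition remains. This stands, so the figures above are conditional.

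A reader might infer that nearly everyone meets the outcome. The documents do not support that. It requires stable sleepers to be coded as change and a stable share of about 0.80 or more, and the protocol gives neither. At shares of 0.50 to 0.60 the outcome is met by 59% to 84%.

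A reader might also infer that a report that improves sleep will look harmful. That too is conditional. Openers must leave the stable group for better sleep, without enough offset from other behaviours. A report that mainly prevents deterioration would look beneficial.

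It is also fair that the authors may have chosen stability because no single direction of sleep change is favourable for everyone, and that an individual threshold could be left to an analysis plan. Neither point explains why an absence-of-change item belongs in a change outcome.

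**Conclusion.** The contradiction is established from the text alone: in 5.2, sleep is scored as absence of change within an outcome defined as "Statistically significant change in at least one of the health care behavior dimensions", against the direction of the other four behaviours and of the stated objective. None of the three codings of the sleep item gives a sound participant-level change outcome.

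The size depends on the reading. If stable sleepers meet a per-person outcome, 50% to 90% of the risk difference from the other four behaviours is lost for assumed s of 0.5 to 0.9, given independence and an equal stable share in both groups. The odds ratio can then move below or above 1, depending on whether the report mainly moves stable sleepers to better sleep or mainly prevents deterioration. If stable sleepers are coded as no change, this dilution disappears but worsening may count as change. If each behaviour is tested separately, only the sleep result is affected.

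The point concerns a secondary outcome for the third research question. The primary endpoint in 4.1, representativeness, is untouched.

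**What to change.** In 5.2, take sleep stability out of the at-least-one outcome and report it separately. This is sound under every reading.

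If sleep is to stay in, score it as an individual-level favourable change, with a pre-stated threshold and a pre-stated direction relative to the participant's baseline sleep duration, and count unfavourable changes separately. The threshold should fit the sleep item actually used, because the text shown does not say whether it is categorical.

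In either case, form the at-least-one outcome only from dimensions coded in the same direction, and state whether it is a per-person variable or five separate analyses. The cost is a few sentences in 5.2 and no new data. It should be settled before the behaviour data are analysed, so that the coding is not chosen after results are seen.

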  1. INTERVENTION

In addition to filling out the survey questions at four points in time (intervention 1), all participants will receive PRO feedback as a potential nudge (intervention 2). The PRO feedback will be a pdf report sent via email and available in their study participant profile, which graphically (line charts) shows the patients’ individual generic and disease-specific health status in comparison to the individual peer group. In addition to the visual feedback, the results will shortly be explained on the same page. The description will cover whether patient-individual PRO scores are better or worse compared to the peer group, and for longitudinal values, whether patient-related changes improved or worsened. Additional details on the scores, sub-scores, and calculations are shared with the patients on the following pages of the report. Peer groups are classified according to their disease, gender, and age group. The peer group is created based on individuals who have replied to the previous survey and will only be displayed if the group consists of at least four individuals. This threshold is set by the German General Data Protection Regulation. The report refers to the patients’ physicians as the main contact to discuss the results or in case of questions.

- 1. SAMPLE SIZE

The sample is drawn stratified randomly from insured patients of one large German statutory health insurance with about 9 million insured persons (of about 73 million statutorily insured persons in total in Germany) according to their diagnosis and/or disease management program status. A one-to-one matching of participants of one DMP with non-participants of a DMP but with the same proven diagnosis according to the ICD-10-GM system is made. Further stratification criteria are age group, gender, and health system utilization.

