  1. OTHER PARAMETERS

**Demography and Baseline**

See Secondary Parameter Outcomes in 4.2.

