**Subgroup analysis**

Subgroup analyses will be conducted by all patient characteristic variables under 4.2. Height & weight will be combined to BMI according to WHO standards. Additionally, subgroup analyses will be performed by DMP membership and healthcare utilization. Subgroup analyses cover all study participants as well as analyses of each chronic disease population.

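### The planned analysis of emotional reaction never separates worse-than-peer reports, so as written it does not answer the protocol's own question about them

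*Protocol*

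**What the plan says.** Among the questions on benefits and drawbacks of PRO feedback, section 1.2 of the protocol asks: "Are there any negative emotional reactions when receiving PRO feedback that shows values worse than those of a comparable group"? The question concerns people whose report was unfavourable.

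The variable needed to identify them is produced by the study. Section 2.4 says of the text in the report: "The description will cover whether patient-individual PRO scores are better or worse compared to the peer group". Section 2.6 lists "Emotional reaction to PRO feedback" among the patient-reported indicators, and also whether the participant looked at the feedback.

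The analysis is in section 5.2, under PRO feedback. After the main item on behaviour change it plans a "Descriptive exploratory analysis of the rates of the following two evaluation dimensions and statistically significant differences in subgroups (see 5.1 and 4.3"), and then lists understandability, helpfulness and emotional change. The subgroups are defined elsewhere:

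- Section 5.1: "Subgroup analyses will be conducted by all patient characteristic variables under 4.2".
- Section 5.1, next: "Additionally, subgroup analyses will be performed by DMP membership and healthcare utilization".
- Section 4.3 on demography and baseline adds nothing of its own: "See Secondary Parameter Outcomes in 4.2".

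The outcomes that section 4.2 gives for the third research question are comprehensibility, helpfulness and impact on behaviour. Emotional reaction is not among them.

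**The concern.** The objective is conditional on what the report showed, but the analysis conditions only on who the patient is. A pooled rate of negative reactions mixes people who were told they do better than their peers with people who were told they do worse. If reactions are concentrated in the second group, the pooled rate understates them, and a low overall figure could be read as reassurance on a question it does not address.

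This matters because emotional reaction is the item aimed most directly at a drawback of the feedback. The behaviour endpoints in section 5.2 count favourable shifts or, for sleep, stability.

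**Working it through.** **1. Tracing the subgroups.** The cross-references in 5.2 resolve as follows.

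| Source | Grouping variables |
|---|---|
| 4.2, all segments | age, gender, type of chronic disease, DMP participation |
| 4.2, responder groups | BMI, education, profession, household size, household income |
| 5.1, added | DMP membership, healthcare utilization |
| 4.3 | refers back to 4.2 only |

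Whether the report was better or worse than the peer group appears nowhere in this list. Section 5.2 does name a contrast based on the feedback, "comparison of participants who opened the report vs. those who did not, using logistic regression (change/no change"), but it is attached to behaviour change and concerns opening the report, not its content.

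**2. Whether the listed subgroups could stand in for report content.** Section 2.4 forms peer groups by disease, gender and age group. Three of the main subgroup variables are therefore the ones within which each patient is compared. Each such subgroup can be expected to contain both better- and worse-than-peer recipients, so splitting by them does not isolate the second kind. The other variables may correlate with report content, but they are proxies for something the study records directly.

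**3. What a pooled rate says about the group asked about.** Let w be the share of reports that are worse than peers, P the pooled rate of negative reaction, and r the rate among worse-than-peer recipients. Then P = w·r + (1 − w)·s, where s is the rate in everyone else. Since s lies between 0 and 1, r lies between max(0, (P − (1 − w))/w) and min(1, P/w). The protocol gives neither P nor w. Assuming P = 10%:

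| w (assumed) | Lower bound for r | Upper bound for r |
|---|---|---|
| 30% | 0% | 0.10/0.30 = 33% |
| 50% | 0% | 0.10/0.50 = 20% |
| 70% | 0% | 0.10/0.70 = 14% |

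The lower bound is 0 in each row because P is smaller than 1 − w.

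Dilution can be shown with assumed rates of r = 20% and s = 2%. With w = 50% the pooled rate is 0.5 × 20% + 0.5 × 2% = 11%. With w = 30% it is 0.3 × 20% + 0.7 × 2% = 7.4%. The contrast between 20% and 2% is an input here, not an estimate.

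**4. Whether the data could support the missing contrast.** The protocol's expected number of complete data sets reproduces: 200,000 × 0.30 = 60,000; 60,000 × 2/3 = 40,000; 40,000 × 0.40 = 16,000. Split 16,000 by report content, assume negative-reaction rates of 12% (worse) and 10% (not worse), and use the two-sided 0.05 level of section 5.1. Power is Φ((0.02 − 1.96·SE₀)/SE₁), with SE₀ from the pooled proportion and SE₁ from the separate proportions.

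| w (assumed) | n worse / not worse | SE₀ | SE₁ | Power |
|---|---|---|---|---|
| 30% | 4,800 / 11,200 | 0.00531 | 0.00548 | 96% |
| 50% | 8,000 / 8,000 | 0.00495 | 0.00494 | 98% |
| 70% | 11,200 / 4,800 | 0.00548 | 0.00531 | 96% |

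These figures treat all 16,000 as having looked at a report that can be classified. Unread, mixed or peer-less reports would lower them. They show only that the contrast is within the study's reach.

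**The case against.** Several points on the other side have weight.

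- **The SAP is not shown, and strata for an exploratory item are often set there.** This is true in general. Here, though, the protocol is not silent: it states an analysis and names its subgroups by cross-reference, and those do not match the objective. A SAP may repair this, but the mismatch within the protocol remains.
- **The data-analysis list in 5.2 allows regressions with other collected variables, depending on the research question.** That clause concerns variables to control for, chosen because they are significant. It names neither emotional reaction nor report content, so it leaves room for the contrast without supplying it.
- **The questionnaire item may itself refer to the comparison with peers.** The figure with the survey items is not shown, so this cannot be excluded. It would change what the item measures. The analysis would still not be grouped by what the report showed.
- **Classifying reports is not trivial.** This stands. A report covers generic and disease-specific status, and coronary artery disease has two disease-specific scores, so one report can be better on one score and worse on another. Emotional reaction is listed as one item, so a reaction cannot be attributed to a single score. Section 2.4 also displays the peer group only if it has at least four members, so not every report carries a comparison.
- **The magnitude rests on assumed rates.** This also stands. The figures in the working show how little a pooled rate reveals, not how large the problem is here.

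A reader might infer that emotional reaction is the study's only harm measure, because Safety is marked not applicable. That goes too far: helpfulness, comprehensibility and the depression domain within PROPr also bear on drawbacks. Emotional reaction is only the most direct measure.

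**Conclusion.** The point holds in a limited form. As written, the analysis of emotional change in section 5.2 does not answer the question in section 1.2, because it never conditions on whether the report was worse than the peer group. The size cannot be taken from the protocol. With an assumed pooled rate of 10%, the rate in the group asked about is bounded only between 0% and 14–33%, depending on an assumed share of worse-than-peer reports of 70% down to 30%.

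Two stronger readings are not supported. A reader might infer that the question cannot be answered at all. It can: emotional reaction, the scores, whether the report was looked at, and the better/worse statement are all produced by the study. A reader might also infer that the study asks whether an unfavourable report causes negative emotions. Section 1.2 asks only whether such reactions occur on receipt. As all participants receive feedback, there is no no-report control, and even the corrected analysis gives an association.

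The objective is secondary and the item exploratory. The correction is still worth making, because it concerns a stated question about a possible drawback and needs no new data.

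**What to change.** In section 5.2, report the rate of negative emotional reaction among participants who looked at a report showing worse-than-peer values, and compare it with the rate among those whose report showed better values. Use the better/worse statement in the report that preceded the answer. Classify by the generic score and by the disease-specific score. Add a separate category for mixed results and another for reports without a displayed peer group (fewer than four individuals). State that the contrast is an association.

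In section 4.2, add emotional reaction to the outcomes for the third research question. In section 5.2, correct the announced number of evaluation dimensions from two to three.

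The cost is one extra set of exploratory tables and a simple written rule for mixed reports, including how the two coronary artery disease scores are combined. No further data collection is needed.

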**Data analysis**

- Check for normality using the Shapiro–Wilk test
- Check for intraclass correlation using intraclass correlation coefficients
- Analyze missing data
- Descriptive statistics of patient and treatment characteristics
- Time series analysis
- Parametric and non-parametric methods
- Statistical tests depending on normality for the primary and secondary outcomes to compare:
  - Responders vs. non-responders (to the nudge)
  - DMP vs non-DMP members
- Linear and logistic regressions controlling for:
  - Significant patient characteristics
  - Significant other collected variables depending on the research question

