   1. STUDY DESIGN

The study is an observational prospective cohort study with patients of four chronic disease areas with existing DMPs (asthma, chronic obstructive pulmonary disease (COPD), diabetes (type 1 and type 2) and coronary artery disease) with two sub-cohorts (DMP and non-DMP) for each disease.

- Type of control: none / group matched BARMER insurees (matching criteria: disease area, gender, age group)
- Level and method of blinding: none
- Method of treatment assignment: stratified randomized selection of study population
- Number of subjects: 200,000 patients invited (50,000 per chronic indication and about 25,000 in each sub-cohort)
- Duration of study: one year (four quarterly survey periods)

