An initial invitation letter is sent to 200,000 insured individuals, 50,000 of each of the selected chronic conditions (about 25,000 per sub-cohort). Diabetes type 1 and type 2 are considered jointly as there is no differentiation in the selected PROMs. The patients of all chronic diseases are allocated to groups based on their participation in DMP (DMP or non-DMP group). Prior experiences suggest that around 30% of patients react to invitations to participate in research by their insurer [29-31]. Two-thirds of initial participants are expected to allow follow-up contacts and around 40% of these patients will continue participating in all the follow-up surveys after receiving reminders for each task. Therefore, after accounting for non-participants and participants with no complete survey data we expect a complete data set for 16,000 participants. However, the first research question will investigate response rates as there is no evidence on this population yet.

- 1. STUDY PROCEDURE

Eligible participants will be participating in the study for a maximum of four quarters, starting with the first access of the digital questionnaires followed by quarterly digital surveys split into several tasks. To start the survey, participants register with their study pseudonyms and share personal information, e.g., basic demographics and identification data. Each survey period contains four tasks to be completed by participants defined as sets of questions that each will take five to ten minutes to complete. The participants are invited to answer PROM and PREM surveys.
[figure not shown]

*Figure 1: Study design: Participants’ timeline and tasks*

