   1. GENERAL METHODOLOGY

Quantitative variables will be described as mean (respectively median), standard deviation (inter-quartile range), number, and rate of missing data, and compared between arms with a t-test, or if not appropriate with a Wilcoxon rank-sum test. Qualitative variables will be reported as absolute and relative frequencies, number, and rate of missing variables, and compared between sub-cohorts with the Chi-square test or the Fisher’s exact test. Variables will be compared between both sub-cohorts (DMP and non-DMP participants). P-value <0,05 with a bilateral hypothesis will be considered significant. All the analyses will be carried out using R, SAS, and other statistical software for Windows.

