**Secondary Outcomes**

Value of care:

Value of care delivery is assessed according to the Porter value-based healthcare framework:

Patient-Value = Outcome/Costs

In the analysis, we will firstly focus on the outcome side of the value equation and assess the outcome side based on PROMs and PREMs. The categorization into suspected high-value and suspected low-value care is hence based on PROMs and PREMs. Outcomes higher than average in at least two survey periods are classified as suspected high-value care whereas outcomes lower than average in at least two survey periods are classified as suspected low-value care. Outcomes not included in one of the categories will be separated and excluded from analysis (see Figure 4).

[figure not shown]

*Figure 4: Assessment of Value-Based Healthcare - Outcome dimension*

|  | **PROM – outcome (health)** | **PREM – outcome (responsiveness)** |
| --- | --- | --- |
| **Suspected low-value care** | Maximum one standard deviations above average in at least two survey periods | Maximum one standard deviations above average in at least two survey periods |
| **Suspected high-value care** | Maximum one standard deviations below average in at least two survey periods | Maximum one standard deviations below average in at least two survey periods |
| **Measure-ment** | Separately for health-related quality of life (PROPr index score) & disease-specific health (index score of the disease-specific PROM):   - COPD-related health status - Asthma-related health status - Coronary artery disease-related health status - Diabetes-related health status (for both types) | German responsiveness questionnaire index score |

*Table 1: Assessment of Value-Based Healthcare - Outcome dimensions and measurement*

To cover the cost-side of the value equation as well, we add the health care system utilization. For each of the chronic diseases average treatment costs will be calculated. Costs will cover all healthcare related costs (see 2.6 secondary data). Depending on the deviation from the average participants are classified in the following categories:

- Low costs: More than one standard deviation below average in at least two survey periods
- High costs: More than one standard deviation above average in at least two survey periods
- Inconspicuous costs: Else

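### A Shapiro–Wilk check, not the quantity reported, chooses between t-test and rank-sum, so mean score changes and average costs may carry p-values that do not test a difference in means

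*Protocol*

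**What the plan says.** Four parts of the protocol bear on this.

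- **Section 5.2, Data analysis.** The list opens with "Check for normality using the Shapiro–Wilk test" and later has "Statistical tests depending on normality for the primary and secondary outcomes to compare", followed by two contrasts: responders versus non-responders to the nudge, and DMP versus non-DMP members. The same list also names linear and logistic regression.
- **Section 5.1, General methodology.** Quantitative variables are "compared between arms with a t-test, or if not appropriate with a Wilcoxon rank-sum test". The DMP/non-DMP comparison is applied to variables in general. On significance: "P-value <0,05 with a bilateral hypothesis will be considered significant". No separate threshold is given for the normality check.
- **What is reported.** Section 5.2 (Outcome and experience variation) reports the mean change in PROM and PREM index scores, overall and by subgroup. Section 5.3 reports average costs and costs per patient-year, overall and by subgroup. DMP membership is one of the subgroups in section 5.1.
- **Size.** Section 2.1 gives "200,000 patients invited (50,000 per chronic indication and about 25,000 in each sub-cohort"). Section 2.5 expects that "around 30% of patients react to invitations to participate in research by their insurer", that two-thirds of these allow follow-up, and that 40% of those complete every survey.

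**The concern.** A normality pre-test gains power as the sample grows, while the t-test depends less and less on normality. In large groups the rule therefore discards the t-test where it is safe.

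The switch also changes the question. Rank-sum asks whether a value from one group tends to exceed a value from the other. This agrees with a comparison of means when the two distributions differ only by a shift. It need not agree when one group has a wider spread or a longer tail, as cost data may.

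At stake is the match between estimate and p-value. A table could show two nearly equal average costs beside a very small p-value or, in less favourable cases, a significant result in favour of the group with the lower mean.

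**Working it through.** **1. Group size.** The plan's own figure is reproduced first: 200,000 × 0.30 × 2/3 × 0.40 = 16,000. Four diseases with two sub-cohorts each give 16,000 / 8 = 2,000 per sub-cohort, assuming equal response. Those who allow follow-up number 200,000 × 0.30 × 2/3 / 8 = 5,000 per sub-cohort. The calculations below use 2,000.

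**2. How often Shapiro–Wilk rejects** (0.05 level assumed, n = 2,000, 400 simulated samples each; all shapes are assumptions):

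| Data | Rejected |
|---|---|
| Exactly normal | 4.8% |
| Gamma, skewness 0.2 | 91% |
| t with 10 df | 99% |
| Gamma, skewness 0.5 | 100% |
| Integer score 0–20 | 100% |
| Lognormal, log-SD 0.5 or 1.0 | 100% |

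**3. Is the t-test safe here?** For identical lognormal groups of 2,000, Welch's test had a type I error of 5.0%, 3.8% and 4.1% at log-SD 1.0, 1.5 and 2.0 (3,000 runs each). The nominal level is 5%.

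**4. What rank-sum does when spread differs.** Let log-costs in group A have mean 0 and SD 1.0, and in group B mean d and SD s. For a ratio of mean costs r (B to A), d = ln r + 0.5 − s²/2. Then P(A > B) = Φ(−d / √(1 + s²)). The rank-sum statistic is centred near z = (P − 0.5) / √((2n + 1) / (12n²)). For n = 2,000 the denominator is √(4,001 / 48,000,000) = 0.00913. The chance of significance in favour of A is about Φ(z − 1.96).

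*Equal means (r = 1), s = 1.1.* d = 0.5 − 0.605 = −0.105; P = Φ(0.105 / 1.487) = 0.528; z = 3.08; Φ(1.12) = 0.87. Simulation agrees: rank-sum rejects in about 87% of trials and Welch in about 6%.

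*Mean of B truly 10% higher (r = 1.1, ln r = 0.0953):*

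| s | d | P(A > B) | z | Significant for A (wrong direction) |
|---|---|---|---|---|
| 1.0 | 0.095 | 0.473 | −2.94 | 0% |
| 1.05 | 0.044 | 0.488 | −1.33 | 0% |
| 1.1 | −0.010 | 0.503 | 0.28 | 5% |
| 1.15 | −0.066 | 0.517 | 1.89 | 47% |
| 1.2 | −0.125 | 0.532 | 3.48 | 94% |
| 1.3 | −0.250 | 0.561 | 6.63 | 100% |

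Simulations at 2,000 per group agree with these values to within a few percentage points: about 5% at 1.1, 45% to 51% at 1.15, 93% to 96% at 1.2, and 100% at 1.3.

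**5. Scores.** In one simulated example, a skewed 0–20 score with equal means but unequal spread, rank-sum rejected in 54% of trials and Welch in 5%. The mismatch is therefore not confined to costs, although reversal was not calculated for scores.

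**The case against.** The strongest reply is that the protocol never says average costs will be tested by rank-sum. A reader might infer this from "For each of the chronic diseases average treatment costs will be calculated" in section 5.2, but that sentence sets a benchmark for sorting participants into cost categories, and section 5.1 sends categories to chi-square or Fisher tests. Section 5.3 reports average costs but names no test, and its pre/post figures are not a two-sample contrast. **This stands.** Costs reach the rule only through the general comparison in section 5.1 together with the subgroup reporting in section 5.3. Mean PROM and PREM change reaches it more directly, as a secondary outcome.

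Other points in the plan's favour:

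- Several outcomes have their own methods: weighting against a confidence interval for representativeness, logistic regression for PRO feedback, and predictive models for admission. This narrows the scope.
- Linear regression, which estimates mean differences, is also listed, and section 5.1 permits medians. Neither withdraws the rule for the named comparisons.
- No threshold is stated, and the phrase about appropriateness in section 5.1 leaves room for judgement. The automatic switch at 0.05 is an assumption.
- Section 2.5 plans one-to-one matching of DMP with non-DMP members and stratification by age group, gender and utilization. This should reduce differences in spread among those invited. It does not ensure equal spread among those who respond.
- With equal spread, rank-sum finds a true 10% increase more often than Welch (84% versus 64% at 2,000 per group).

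Two stronger readings go too far. The pre-test does not always reject, since exactly normal data fail only about 5% of the time. Nor will cost comparisons necessarily point the wrong way: with a 10% higher mean, reversal is absent at equal spread and common only from about log-SD 1.15 upward.

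**Conclusion.** The point holds as a minor but genuine defect in how the test is chosen. Sections 5.1 and 5.2 let a normality check select the test. At about 2,000 per sub-cohort this will nearly always mean rank-sum for discrete scores and skewed costs, while the reported quantities are means. If spread differs, the p-value does not belong to the reported difference: about 87% rejection by rank-sum against about 6% by Welch when mean costs are equal and log-SD is 1.0 versus 1.1. Significance in the wrong direction, with a 10% higher mean, ranges from 0% to 100% depending on how unequal the spreads are.

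The conclusion rests on four assumptions: a 0.05 threshold for Shapiro–Wilk, equal response across sub-cohorts, lognormal costs, and unequal spread. The documents give no distribution for costs or scores, so the percentages show what can happen and do not forecast this study's results.

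**What to change.** In section 5.2 (Data analysis), remove normality as the rule that decides the test, and align section 5.1 with it. Suggested wording: *Where a mean is reported (change in PROM or PREM score, costs), sub-cohorts are compared by Welch's t-test or by regression with robust standard errors, with the mean difference and its 95% confidence interval. Rank-sum tests are reported as a sensitivity analysis and labelled as comparing distributions, not means. Shapiro–Wilk results, if shown, are descriptive only.*

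Section 5.3 should say whether average costs are compared between sub-cohorts and, if so, by this method.

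The cost is a change of wording. It needs no new data and slightly less analysis. Where spreads are equal, rank-sum is the more sensitive test for skewed costs, and keeping it as a sensitivity analysis preserves that information.
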